## 1.2 Certificate History

| Date              | Action                          |
|-------------------|---------------------------------|
| 03 January 2013   | Amulet CE Mark                  |
| 23 September 2014 | Change in Amulet delivery cable |

## 2. BACKGROUND AND JUSTIFICATION

The loss of mechanical efficiency during atrial fibrillation (AF)\* leads to insufficient contraction in the left atrium (LA). Stagnation of blood flow in the LA leads to hypercoagulability and thus increased risk for thrombus formation in the LA or LAA. Approximately 90% of all thrombi in subjects with NVAF forming in the LA originate in the LAA. The thrombus formation, in turn, exposes the subject to thromboembolic events. Approximately 6% of embolic events result in peripheral embolism as opposed to ischemic stroke.

Echocardiographic risk factors for LAA thrombus formation include echocardiographic evidence of decreased LAA flow velocity and spontaneous echo contrast within the LA and LAA. The normal flow pattern of the LAA is the ejection of blood from the appendage following atrial contraction at a velocity greater than 40cm/s. Agmon et al. found that the relative risk reduction of ischemic stroke was 2.6 times greater in subjects with LAA flow velocities < 20 cm/s than those with higher LAA velocities.

Ischemic strokes in subjects with AF caused major deficits as compared to ischemic strokes in subjects with carotid disease. Subjects with AF had silent infarcts in the SPINAF study in which a CT scan was performed both initially and then again at the end of the average follow-up period of 1.7 years.

Non-valvular AF subjects were assessed to determine the risk of stroke based on the existence of independent risk factors. In a study by Gage et al., the CHADS2 index was found to be the most accurate in predicting the risk of stroke in subjects with AF. The CHADS2 score assigns one point each for the presence of congestive heart failure, hypertension, age greater than 75, and diabetes mellitus and two points for history of stroke or transient ischemic attack (TIA). The study found that AF subjects who were not treated with antithrombotics had an increased risk of stroke from 1.5% to 18.2% based on scores of one and six respectively.

A study by Go et al., reviewed outcome data (11,526 subjects) in a large primary care setting and confirmed that thromboembolic risk increases progressively with CHADS2 score. The study also noted that oral anticoagulation with warfarin reduces the risk of stroke in most subjects with the exception of those at lowest risk (CHADS2 score of zero) and highest risk (CHADS2 ≥ 5) for stroke.

In a meta-analysis conducted by Andersen et al., warfarin was found to be superior to aspirin and placebo in reducing the risk of both stroke and systemic embolism in subjects with NVAF. Hart et al. reported that adjusted dose warfarin reduces stroke by 64% (6 trials) and antiplatelet agents reduce stroke risk by 22%. The study also reported that risk of intracranial hemorrhage was doubled with adjusted dose warfarin compared with aspirin, although the absolute risk increase was by adjusted-dose warfarin vs. control.

Subjects are often poorly compliant with anticoagulation, and anticoagulants are contraindicated in selected subsets of subjects. The reasons given for being contraindicated included prior bleed, patient refusal/preference, high bleeding risk, frequent falls/frailty, need for dual antiplatelet therapy, unable to adhere/monitor warfarin, comorbid illness, prior intracranial hemorrhage, allergy, occupational risk and pregnancy.

*\*See Appendix A for a listing of abbreviations used throughout this document*

Recently, new drugs have been developed with less dietary and pharmacological interactions and less stringent requirements for frequent INR monitoring. Major trials such as RE-LY and ROCKET AF demonstrated that dabigatran and rivaroxiban are non-inferior to warfarin in the prevention of stroke and systemic embolism. The ARISTOTLE Trial demonstrated apixaban was superior to warfarin in preventing stroke or systemic embolism, caused less bleeding, and resulted in lower mortality in subjects with atrial fibrillation. The ENGAGE AF-TIMI 48 Trial demonstrated both once-daily regimens of edoxaban were noninferior to warfarin with respect to the prevention of stroke or systemic embolism and were associated with significantly lower rates of bleeding and death from cardiovascular causes.

Left atrial appendage occlusion (LAAO) is considered a viable alternative to OAC therapy for stroke prevention in patients with NVAF. Evidence supporting LAAO mainly consists of PROTECT AF and PREVAIL, the major randomized studies published to date. Five-year results of PROTECT AF showed superiority of the Watchman device in mortality and stroke reduction compared to optimal medical treatment with warfarin. The Watchman device is constructed of nitinol (a nickel/titanium alloy) and is composed of 10 fixation anchors around the device perimeter that are designed to secure the device in the LAA (Boston Scientific, Minneapolis, MN, USA).

There are several other endocardial LAAO devices currently in pre-clinical/clinical trial testing phases and one of these (WaveCrest) has CE Mark approval:

- Occlutech LAA Occluder (Occlutech, Helsingborg, Sweden)
- Lifetech LAmbre (Lifetech, Shenzhen, PRC)
- Sideris Transcatheter Patch (Custom Medical Devices, Texas, USA)
- Ultrasept (Cardia, Eagan, MN, USA)
- Pfm ((Pfm Medical, Inc., Carlsbad, CA, USA)
- WaveCrest LAAO (Coherex Medical, Salt Lake City, UT, USA)

#### AMPLATZER™ Cardiac Plug and the AMPLATZER™ Amulet™ device

Both the AMPLATZER Cardiac Plug (ACP) and AMPLATZER Amulet devices have CE Mark approval. The ACP device (St Jude Medical, St. Paul, MN, USA) is a self-expandable nitinol device, with fixation anchors. The ACP device is a first generation device based on AMPLATZER occluder technology specifically designed for LAAO. Refer to the Investigator's Brochure (**Appendix D**) for data published on the ACP device.

The ACP device demonstrated favorable feasibility and safety results in observational studies in Europe. [name] article details an investigator-initiated retrospective data collection to evaluate and demonstrate the initial European experience in patients treated with the ACP device between December 2008 and November 2009. Favorable ACP registry study results were presented at EURO PCR in 2012 and 2014.

The Amulet device is a second-generation ACP device. To date there have been two single center self-reported studies of initial use of the Amulet device. The first reported use by Lam et al. involved a retrospective review of 17 subjects from implant to 90 days follow-up at the Cardiovascular Center in Frankfurt. The second reported use by Freixa et al. involved 25 subjects enrolled at Barcelona University and patients were followed for 3 months. Both of these single center studies report high

implant success rates however, long-term safety and efficacy analysis were not conducted due to the short follow up period.

Results from a multicenter study involving 22 sites, 1,047 consecutive patients and the ACP device showed high procedural success and a favorable outcome for the prevention of AF-related thromboembolism^33.

The aim of this observational post-market study is to compile real world outcome data on the use of the CE marked Amulet device in NVAF subjects.

### **3. RISKS AND BENEFITS**

#### **3.1 Anticipated Clinical Benefits**

For subjects who can take OAC medication the potential benefit is that subjects may not need to be on long-term warfarin, or other OAC therapy and thus will not be exposed to associated complications. This device may also provide potential benefits to subjects who cannot take OAC. Subjects who receive the device may also experience a decrease in the associated risk of thromboembolism.

#### **3.2 Anticipated Adverse Events and Adverse Device Effects**

Anticipated adverse events and adverse device effects may occur during and after the Amulet device implant procedure. Serious adverse event definitions are provided in Section 8.

#### **3.3 Risks**

The risks associated with the Amulet device implant procedure are similar to those of other cardiac catheterization procedures. Radiation risks associated with the procedure are comparable to a diagnostic catheterization procedure.

The risks associated with the implanted Amulet device are similar to other implantable cardiac LAAO devices. Refer to Section 8 for a complete list of potential anticipated serious adverse events, which are also included in the IFU included in the Investigator's Brochure (**Appendix D**).

#### **3.4 Risk to Benefit Rationale**

Percutaneous LAAO offers an alternative to physicians who are caring for patients with AF who are at high risk for both bleeding and stroke.

#### **3.5 Residual Risks Associated with the Device**

The Amulet device is market approved in all the countries where the study will be conducted. The risk profile of the Amulet device implant procedure is described in the labeling for the CE marked device, the risk analysis report, the IFU (included in the IB in **Appendix D**), and Section 8 of this protocol. The overall events from a risk perspective are similar to the risks with minimally invasive implantable therapies. Complication rates are within expected ranges and the risk/benefit profile is similar to alternate therapies.

#### **3.6 Steps to Control or Mitigate Risks**

The Sponsor will select investigators qualified by training and experience to participate in this study. Participating sites will be selected based upon qualifications of the primary investigator. During the study, sites may be subject to quality assurance audits by the Sponsor (or designee), as

well as monitoring visits to assess data integrity and study compliance. Additionally, the study will have an appointed independent Clinical Event Committee (CEC) that will review and adjudicate all reported serious adverse events. Any additional risk is mitigated with vigilance reporting for a CE marked product.

## **4. STUDY DESIGN**

### **4.1 Purpose**

The Amulet device is a transcatheter, self-expanding nitinol device intended for use in preventing thrombus embolization from the LAA. The purpose of the Amulet observational post-market study is to compile real world outcome data on the use of the CE marked Amulet device in NVAf subjects.

### **4.2 Study Design and Scope**

The Amulet device will be clinically evaluated through this observational post-market study. The study design is a prospective, multicenter, non-randomized observational post-market study, where all subjects eligible for enrollment will receive the Amulet device.

#### **4.2.1 Subject population**

The subject population will include participants that are  $\geq 18$  years old and diagnosed with NVAf.

#### **4.2.2 Number of study subjects**

Approximately 1000 subjects will be enrolled in the study at up to 75 sites in EMEA, ANZ, Latin America, and AP. A list of clinical investigation sites and ECs will be kept under separate cover and is available upon request (**Appendix F**).

#### **4.2.3 Enrollment period and study duration**

Enrollment in the study will be complete within approximately 24 months of the first subject enrollment. As the study requires follow-up visits through at least 2 years, the total study duration is expected to be 4 years.

## **4.3 Objectives**

### **4.3.1 Primary objectives**

The Amulet observational post-market study has four primary objectives:

1. Assessment of acute (0 - 7 days post procedure) serious adverse events
2. Assessment of late (> 7 days post-procedure) serious adverse events through 2 years
3. Report the percentage of stroke (ischemic), systemic embolism, and cardiovascular death through 2 years
  - Cardiovascular death is defined as (see **Appendix L**) death due to proximate cardiac cause, death caused by non-coronary, non CNS vascular conditions, death from vascular CNS causes, hemorrhagic stroke, ischemic stroke, all procedure related deaths, sudden or unwitnessed death and death of an unknown cause

4. Report the percentage of bleeding events through 2 years

#### **4.3.2 Secondary objectives**

The Amulet observational post-market study has three secondary objectives:

1. Technical success – successful implantation of the Amulet device in the LAA
2. Procedural Success – technical success and the absence of major adverse events during hospitalization. Major adverse events include death, stroke, embolism, pericardial or other major bleeding requiring intervention, device embolization, and major vascular complications
3. Report percentage of subjects taking OAC and antiplatelet drugs through 2 years

#### **4.4 Inclusion and Exclusion Criteria**

Subjects, who meet all of the inclusion criteria and none of the exclusion criteria, are eligible to participate in this study.

All subjects who sign the informed consent will be assigned a study identification number and this will be recorded on an Inclusion/Exclusion electronic case report form (eCRF). The subject ID number will be unique to each individual and will allow the participant to be linked if necessary, to name, alternative identification or contact information. To ensure subject privacy and confidentiality of data, subject ID numbers will be used and maintained by study site personnel for the duration of the study.

##### **4.4.1 Inclusion criteria**

To participate in this clinical study, the subject must meet all of the following four inclusion criteria:

1. Subject with a history of paroxysmal, persistent or permanent NVAf
2. Subject who is 18 years or older, or of legal age to give informed consent specific to state and national law
3. Subject who is eligible for an Amulet LAAO device according to current international guidelines and per physician discretion
4. Subject who is willing and capable of providing informed consent, participating in all testing associated with this clinical study

##### **4.4.2 Exclusion criteria**

Subjects are not eligible for clinical study participation if they meet any of the following six exclusion criteria:

1. Subject with evidence of an intracardiac thrombus
2. Subject with active infection or active endocarditis or other infections producing bacteremia
3. Subject where the placement of the device would interfere with any intracardiac or intravascular structures

4. Subject with any medical disorder that would interfere with completion or evaluation of clinical study results
5. Women of childbearing potential who are, or plan to become, pregnant during the time of the study (method of assessment per physician discretion)
6. Subject with LAA anatomy that does not accommodate a device per the sizing guidelines

#### **4.5 Informed Consent Process**

The process for obtaining informed consent must comply with the ethical principles defined in the current version of the Declaration of Helsinki (**Appendix C**).

Prior to enrollment in the clinical study, all subjects will be consented, as required by applicable regulations and the site's ethics committee (EC). Informed consent must be obtained from each subject prior to the device implant procedure. The consent form must be signed and dated by the subject and by the person obtaining the consent, where applicable.

The principal investigator (PI) or his/her authorized designee will conduct the informed consent process. This process will include a verbal discussion with the subject on all aspects of the clinical study that are relevant to the subject's decision to participate, and the subject should be allowed adequate time to review and ask questions.

Documentation that informed consent was obtained will be recorded on the eCRF and in the subject's medical record. The signature date on the consent form should be referenced. The original signed informed consent should be filed in the subject's study chart and a copy of the signed consent form given to the subject per EC requirements.

A template of the informed consent form is provided in **Appendix G**. Any changes to the template must be approved by SJM prior to ethics committee review and approval.

A subject cannot be consented to the study prior to EC approval of the informed consent form. The subject shall be provided the informed consent form that is written in a language understandable to the subject and has been approved by the site's EC.

The subject is enrolled in the study when consent has been obtained and the dilator/delivery system is introduced. Failure to obtain informed consent from a subject prior to study enrollment must be reported to SJM as soon as possible and to the reviewing site's EC consistent with the site's EC reporting requirements.

## **5. DEVICE**

### **5.1 Device Description**

The Amulet device (**Figure 1**) is constructed from a nitinol mesh and consists of a lobe and a disc connected by a central waist. The lobe ranges in diameter from 16 to 34 mm (**Table 1**) and has stabilizing wires for device placement and retention. The disc is larger in diameter than the lobe, ranging from 20 to 41 mm; both the disc and the lobe contain polyester fabric to facilitate LAAO. There are threaded screw attachments at either end of the device for connection to the delivery and loading cable. Radiopaque markers at either end of the device and at the location of the stabilizing wires allow for predictable placement of the device. The stabilizing wires and polyester patch are

secured to the device using polyester thread. A platinum/iridium thread is attached to the nitinol braid.

Accessories packaged with the Amulet device include the loader, loading cable, loading cable vise, delivery cable, delivery cable vise, and hemostasis valve. The Amulet device is recommended for delivery using the AMPLATZER TorqVue 45 x45 Delivery Sheath (12F and 14F). Refer to the Investigator's Brochure (IB) (**Appendix D**) which includes the IFU for additional information.

**Figure 1: The Amulet device and key components**

[figure not shown]

**Table 1: Model numbers and key dimensions of the Amulet device and delivery system**

| Part Number    | Amulet Device Size | Left Atrial Disc Size (mm) | Lobe Length (mm) | # of stabilizing wires | TorqVue Delivery System |
|----------------|--------------------|----------------------------|------------------|------------------------|-------------------------|
| 9-ACP2-007-016 | 16mm               | 22                         | 7.5              | 6                      | 12F*                    |
| 9-ACP2-007-018 | 18mm               | 24                         | 7.5              | 6                      | 12F*                    |
| 9-ACP2-007-020 | 20mm               | 26                         | 7.5              | 8                      | 12F*                    |
| 9-ACP2-007-022 | 22mm               | 28                         | 7.5              | 8                      | 12F*                    |
| 9-ACP2-010-025 | 25mm               | 32                         | 10               | 8                      | 12F*                    |
| 9-ACP2-010-028 | 28mm               | 35                         | 10               | 10                     | 14F                     |
| 9-ACP2-010-031 | 31mm               | 38                         | 10               | 10                     | 14F                     |
| 9-ACP2-010-034 | 34mm               | 41                         | 10               | 10                     | 14F                     |

*\*Per the IFU, if a 14 Fr delivery sheath is selected for use with a 16 mm-25mm device, tightly connect the 14 Fr sheath adaptor to the delivery sheath hub*

## 5.2 Device Accountability

The Amulet device has CE Mark approval and is market released in the countries where this study will take place. Therefore, there are no additional tracking requirements for this study. Information regarding opened, introduced, and implanted devices will be recorded on the Procedure eCRF.

## 6. STUDY PROCEDURES

This study will be conducted in accordance with the clinical protocol and IFU included in the IB (**Appendix D**). All persons participating in the conduct of the study will be qualified by education, training, or experience to perform study-related tasks.

The study will not commence until SJM receives written approval from the EC and relevant regulatory authorities, and all required documents have been collected from the participating sites.

**Figure 2** below describes the study flowchart for subject screening, consent, enrollment and follow-up through the 2-year follow-up visit. **Table 2** below outlines the testing and assessments required per study visit interval. **Table 3** below outlines the eCRFs to be completed for enrolled subjects that receive the device, and as per the recommended study visit intervals.

[figure not shown]

**Figure 2: Study flowchart for subject screening, consent, enrollment and follow-up**

**Table 2: Study visits and activities**

| Study Activity                                                                                                                    | Visit | Enrollment & Baseline | Procedure        | Discharge | 1-3M | 6M Phone Visit (+/- 2 weeks) | 12M (+/- 6 weeks) | 24M Phone Visit (+/- 12 weeks) | Interim Follow-up |
|-----------------------------------------------------------------------------------------------------------------------------------|-------|-----------------------|------------------|-----------|------|------------------------------|-------------------|--------------------------------|-------------------|
| Informed Consent Process                                                                                                          |       | X                     |                  |           |      |                              |                   |                                |                   |
| - History and physical
- Cardiovascular and medical exam
- CHA 2 DS 2 -VASc score
- HAS-BLED score |       | X                     |                  |           |      |                              |                   |                                |                   |
| 12-lead ECG                                                                                                                       |       | X                     |                  |           |      |                              |                   |                                |                   |
| Pregnancy Test                                                                                                        |       | X                     |                  |           |      |                              |                   |                                |                   |
| Medication Assessment                                                                                                             |       | X                     |                  | X         | X    | X                            | X                 | X                              | X                 |
| Modified Rankin Scale                                                                                                 |       | X                     |                  |           |      |                              |                   |                                | X     |
| Angiography                                                                                                                       |       |                       | X                |           |      |                              |                   |                                |                   |
| TTE                                                                                                                               |       |                       |                  | X         |      |                              |                   |                                |                   |
| TOE                                                                                                                               |       | X         | X  |           | X    |                              |                   |                                | X     |
| ICE                                                                                                                               |       |                       | X    |           |      |                              |                   |                                |                   |
| Adverse Event Assessment                                                                                                          |       |                       | X                | X         | X    | X                            | X                 | X                              | X                 |

Pregnancy test for women of childbearing potential

Perform additional Modified Rankin Scale assessment 90 days after a confirmed stroke or TIA

CT may be used as additional information and performed complimentary to the TOE, per institutional standard of care

Complete if stroke or TIA is confirmed

The Baseline TOE is optional if a TOE is performed on the day of procedure to rule out the presence of intracardiac thrombus (including left atrial appendage thrombus) and to assess the size and shape of the LAA

ICE may be performed for placement of the device in a sub-set of centers pre-approved by SJM (see **Appendix K**)

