## **6.6 Subject Study Completion**

After the 2-year follow-up visit is completed, subjects will be discontinued from the study and return to receiving medical care per their physician's recommendations.

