#### **8.1.2 Assessing, recording and reporting serious adverse events, serious adverse device effects, and device deficiencies/complaints**

Safety surveillance within this study and the safety reporting performed both by the investigator and Sponsor starts as soon as the dilator/device delivery system has been introduced. The safety surveillance and the safety reporting will continue until the last visit has been performed, the subject is deceased, the subject/investigator concludes their participation into the study or the subject/investigator withdraws the subject from the study.

All serious adverse events (including deaths), serious adverse device effects, and device deficiency information (if applicable) will be collected throughout the clinical study and reported to the Sponsor. Investigators will record all serious adverse events, serious adverse device effects, and deaths on the appropriate eCRF. Device deficiencies will be reported per country reporting timeline requirements to the Sponsor outside of the database on an Event Report Form (**Appendix I**).

For any serious adverse event (including deaths) and any serious adverse device effect, the investigator shall notify the Sponsor immediately of the investigator's awareness of the event and provide the Sponsor with all necessary documentation needed. Device deficiencies will be reported to the Sponsor outside of the database on an Event Report Form (**Appendix I**), as soon as possible after first learning of the event.

Records relating to the subject's subsequent medical course must be maintained and submitted (as applicable) to the Sponsor until the event has subsided or, in case of permanent impairment, until the event stabilizes and the overall clinical outcome has been ascertained. Additional

information may be requested, when required, by the Sponsor in order to support the reporting of serious adverse events to the CEC, regulatory authorities and/or other authorities.

Serious adverse events and serious adverse device effects should be monitored by the investigator until resolved. The status of the subject's condition should be documented at each follow-up visit.

Events reportable to the Sponsor, EC, CAs and regulatory authorities (as applicable) include:

- All serious adverse device effects
- All serious adverse events (including deaths and whether or not the event is considered device or procedure related)

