## **12. STATISTICAL METHODS**

No formal hypothesis will be tested for this observational post-market study. However, point estimates and exact 95% confidence intervals will be provided for the following rates in the study:

- Procedural serious adverse events (0 - 7 days) post procedure or before hospital discharge whichever latest) will be summarized for all subjects as well as stratified by imaging modality used for implanting the device (TOE and ICE)
- Late serious adverse events through 2 years
- Occurrence of ischemic stroke , systemic embolism and cardiovascular death through 2 years
- Occurrence of bleeding (including hemorrhagic stroke) events through 2 years

Data collected on the following objectives will also be reported:

- Technical success (secondary objective)
- Procedural success (secondary objective) - This objective will be summarized for all subjects as well as stratified by imaging modality used for placement of the device (TOE and ICE)
- OAC usage through 2 years (secondary objective)

- Serious Adverse Events – this may include, but is not limited to:
  - Significant bleeding events (e.g. cardiac tamponade, central nervous system (CNS) bleeding, and any bleeding related to the device or procedure that necessitates an operation)
  - Endocarditis
  - Device embolization (summarized by those that can be snared, and those that require surgical intervention)
  - Thrombus on device
  - All strokes
  - Transient ischemic attacks
  - Systemic embolism
  - Cardiovascular death
- Closure at procedure and 1-3 months post implant
  - The echo core lab's adjudication of residual flow will be used for this analysis. The following guidelines will be used:
    - None – No color flow jet in or out of the LAA
    - Small leak: < 3 mm diameter jet by color flow Doppler
    - Medium leak: 3-5 mm diameter by color flow Doppler
    - Large leak: > 5 mm diameter jet by color flow Doppler

Other variables may be summarized as deemed appropriate. The numerator for all rates will be the number of subjects who experience the corresponding event. The denominator for all rates will be subjects who experience the corresponding event plus all other subjects who achieve 2-years of follow-up.

Version 9.0 or higher of the SAS® statistical software package or other widely accepted statistical software will be used to provide all statistical analyses. Unless otherwise stated, attempts will not be made to adjust for multiple comparisons.

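### The final contact may fall up to 12 weeks before 24 months and ends event collection, so up to 84 of the 730 days behind the 2-year rates can go unobserved

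*Protocol*

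**What the plan says.** Table 2 gives the final contact as "24M Phone Visit (+/- 12 weeks"); the synopsis gives the same window. It is a telephone contact for medication and adverse events, and no later contact is scheduled.

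The end of observation is tied to that contact. Section 6.6 states: "After the 2-year follow-up visit is completed, subjects will be discontinued from the study". Section 8.1.2 states: "The safety surveillance and the safety reporting will continue until the last visit has been performed", with death or withdrawal as the other end points. Section 6.1 likewise stops SAE reporting when the subject concludes the study.

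The horizon of the results is 2 years. Section 4.2.3 says: "As the study requires follow-up visits through at least 2 years". Section 12 lists, for example, "Occurrence of ischemic stroke , systemic embolism and cardiovascular death through 2 years", with late SAEs and bleeding over the same period.

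Section 12 also fixes how the rates are formed. The numerator is a count of subjects with the event in question. On the other half of the fraction it says: "The denominator for all rates will be subjects who experience the corresponding event plus all other subjects who achieve 2-years of follow-up". It does not say in days what achieving 2 years means.

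**The concern.** The window is symmetric, but its consequences are not. A call made late still covers the full 2 years. A call made early closes the record before 2 years have passed. The early call is in window, so it does not trigger the out-of-window protocol deviation in Table 3, and nothing prompts a second contact.

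The rates for late SAEs, for ischemic stroke, systemic embolism and cardiovascular death, and for bleeding then depend partly on when site staff happen to telephone. The direction of the error depends on an undefined phrase, "all other subjects who achieve 2-years of follow-up":

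- If an in-window visit is enough, early-called subjects count as complete although their last weeks were not observed, and rates come out too low.
- If 730 days are needed, early-called event-free subjects leave the denominator while subjects with events stay, and rates come out too high.

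An analysis plan could settle the definition. It could not supply events between an early last call and day 730, because the protocol stops collecting them.

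**Working it through.** The protocol gives no precision calculation, expected event rate or distribution of call dates, so there is no stated figure to reproduce. The window arithmetic uses the protocol alone; the rates below are illustrations on stated assumptions.

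**Inputs from the protocol:** window of 12 weeks either side of 24 months (synopsis, Table 2); observation ends at the last visit (Sections 6.6 and 8.1.2); numerator and denominator rules (Section 12); about 1000 subjects (Section 4.2.2).

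**Assumptions:** 24 months = 730 days; true 2-year event rate p = 5%; constant hazard; no death, withdrawal or other loss; a share f of subjects called at day 646 and the rest at day 730 or later.

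**1. Window.** 12 × 7 = 84 days. Earliest call: 730 − 84 = day 646. Latest: 730 + 84 = day 814. Largest unobserved part: 84/730 = 11.5%. Other month conventions hardly matter: the earliest day is 636 with 30-day months (720 days) and 647 with 731 days.

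**2. Event probability by day 646.** Daily hazard λ = −ln(0.95)/730. Then p646 = 1 − exp(−646λ) = 4.44%, against 5.00% by day 730.

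**3. Expected counts with N = 1000.**

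- Observed events = N × [f × p646 + (1 − f) × p]
- Event-free subjects with 730 days = N × (1 − f) × (1 − p)
- Visit-completed reading: rate = events / N
- 730-day reading: rate = events / (events + event-free subjects with 730 days)

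| Share called at day 646 | Events | Visit-completed rate | 730-day denominator | 730-day rate |
|---|---|---|---|---|
| 0% | 50.0 | 5.0% | 1000 | 5.0% |
| 10% | 49.4 | 4.9% | 904 | 5.5% |
| 25% | 48.6 | 4.9% | 761 | 6.4% |
| 50% | 47.2 | 4.7% | 522 | 9.0% |

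If all subjects were called at day 646, the visit-completed rate would be 4.4%. With an assumed true 15%, shares of 10%, 25% and 50% give 14.8%, 14.6% and 14.2% on the visit-completed reading and 16.3%, 18.6% and 25.0% on the 730-day reading.

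**4. Calls spread evenly over days 646 to 814.** Half are early and lose 84/2 = 42 days on average, so the cohort loses 0.5 × 42 = 21 days per subject, and 21/730 = 2.9% of follow-up. That equals the average loss in the 25% row (0.25 × 84 = 21 days), so on the visit-completed reading a true 5.0% becomes about 4.86%.

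**5. Scale.** The exact 95% confidence interval for 50/1000 is 3.7% to 6.5%. A shift of 0.14 points is about a tenth of its half-width of roughly 1.4 points.

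**6. With no call before day 730.** Every event-free completer has at least 730 days. Both readings then give 5.0% for a true 5.0%.

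**The case against.** The strongest reply is that the protocol itself calls this contact the 2-year follow-up visit (Sections 6 and 6.6). On that usage, achieving 2 years of follow-up most naturally means completing the in-window visit. Section 12 sets no 730-day threshold, and the phrase in Section 4.2.3 explains the length of the study rather than setting a day count for each subject. The resulting bias is then small, and no hypothesis is tested, so no decision turns on it. This stands, and it sets the size of the point.

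A reader might go further and infer that the 2-year rates could nearly double. The documents do not support that as the expected effect. It needs both the 730-day reading and about half of all calls made at the very start of the window, and the protocol gives no call dates. It also acts entirely through the completer-only denominator. Correcting that rule would remove the upward bias without touching the window, so the two should not be counted as separate harms.

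A reader might also infer that late calls add events up to day 814 to the 2-year rates. The objectives and Section 12 already limit those rates to 2 years, so later events fall outside the stated horizon. Nor would a time-to-event analysis necessarily be biased: if call timing is unrelated to risk, early censoring costs precision only.

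What the reply does not remove is the gap in collection. An unseen analysis plan can define completion, but it cannot recover events the protocol does not collect.

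**Conclusion.** The point holds, at minor to moderate severity. The window, the end-of-participation rule and the 2-year horizon do not fit together: a subject followed exactly as planned can have up to 84 of 730 days (11.5%) unobserved. This follows from the protocol text alone.

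The effect on the rates rests on assumptions about call timing and event rate. On the more natural reading the bias is downward and small: about 4.9% for a true 5.0% with evenly spread calls, and 4.4% at the extreme. On the 730-day reading it is upward, 5.5% to 9.0% for early shares of 10% to 50%; that is the worst case and shares its mechanism with the denominator rule. If few calls are early, both effects are small, but nothing in the protocol keeps them few.

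**What to change.** - In the synopsis and Table 2, change the 24-month window to -0/+12 weeks, so that no final contact is made before day 730.
- In Section 12, state that 2-year rates count events with onset through day 730, and that 2-year follow-up means event status known at day 730 or later.

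The first change closes the gap in collection and makes both readings of the denominator agree. The second makes the cut-off explicit. How deaths and withdrawals before day 730 enter the denominator is a separate matter that this change does not settle.

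The cost is small. The contact is a telephone call, and some calls would be made a few weeks later. Day 814 is already permitted, so the latest possible date for each subject is unchanged.
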